## Abstract

**Background:**

Most cancer patients, under active treatment or not, are sedentary, despite increasing scientific and clinical understanding of the benefits of exercise and physical activity, such as improving quality of life, limiting disease symptoms, decreasing cancer recurrence, and increasing overall survival. Studies have shown that both supervised exercise and unsupervised physical activity programs have low adherence and limited long-term benefits among cancer survivors. Therefore, interventions focused on increasing physical activity levels have clinical and psychological relevance. The present study will examine the feasibility and efficacy of an intervention that combines supervised group exercise with active lifestyle recommendations, analyzing its clinical, psychological, physiological, functional, and immunological effects in breast cancer survivors.

**Methods:**

Women aged 35–75 years who have completed chemotherapy, radiotherapy, and surgery for breast cancer will be recruited from the Cancer Institute of the State of Sao Paulo (ICESP) and take part in a 16-week, parallel-group, randomized, and controlled trial. They will receive a booklet with recommendations for achieving a physically active lifestyle by increasing overall daily movement and undertaking at least 150 min/week of structured exercise. Then, they will be randomized into two groups: the supervised group will take part in two canoeing group exercise sessions every week, and the unsupervised group will increase their overall physical activity level by any means, such as active commuting, daily activities, or home-based exercise. Primary outcome includes aerobic capacity. Secondary outcomes are physical activity, physical functioning, self-reported quality of life, fatigue, presence of lymphedema, body composition, immune function, adherence to physical activity guidelines, and perceptions of self-image.

**Discussion:**

Results should contribute to advance knowledge on the impact of a supervised group exercise intervention to improve aspects related to health, physical functioning, and quality of life in female breast cancer survivors.

**Trial registration:**

Brazilian Registry of Clinical Trials Number: RBR-3fw9xf. Retrospectively Registered on 27 December 2018. Items from the World Health Organization Trial Registration Data Set can be accessed on http://www.ensaiosclinicos.gov.br/rg/RBR-3fw9xf/.

**Supplementary Information:**

The online version contains supplementary material available at 10.1186/s13063-021-05843-z.

## Introduction

Advances in breast cancer diagnosis and therapy have improved the 5-year overall survival rates among these patients, now exceeding 90% in early stages [1–3]. These improved outcomes have called health professionals’ attention to those long-term side effects faced by breast cancer survivors either related to the disease or to their treatment [4–6]. As an example, a substantial fraction of breast cancer survivors does experience long-term side effects that include fatigue, lymphedema, peripheral neuropathy, neurocognitive dysfunction, and persistent pain, as well as an increased risk of developing cardiovascular disease, metabolic disturbances, and compromised mental health (e.g., depression and anxiety) [7–13]. All these aspects negatively affect quality of life of breast cancer survivors. Therefore, non-pharmacological therapies that aim to ameliorate these long-term consequences are critical to improving overall survival and health-related quality of life of breast cancer survivors and should be considered a public health priority. In this sense, the incorporation of healthy and active lifestyle that includes physical activity, weight management, self-care, adequate diet, and nutrition are encouraged [14–21].

The impact of both physical activity and exercise on breast cancer survivors is well documented. The term physical activity applies to any body movement produced by skeletal muscles that increase the energy expenditure, and exercise is considered as a structured physical activity that is undertaken with the purpose of improving health and fitness. In the context of cancer risk and survivorship, physical activity and exercise are linked to reduced risk of cancer recurrence [22, 23], secondary cancers [24], and cancer-specific cardiovascular mortality [25–29]. Indeed, systematic reviews and experimental research clearly describe the positive impact of physical activity and exercise on several aspects of physical and social well-being, and mental health among cancer patients under active treatment or not; or on cancer survivors, including reduced lymphedema, fatigue, depression, and anxiety, while improved cognitive function, cardiovascular fitness, self-esteem, and quality of life [30–36].

The convincing body of basic and clinical studies on the safety and benefits of exercise or physical activity in cancer patients does support the endorsement of post-treatment survivorship guidelines proposed by international organizations for both exercise (e.g., The American College of Sports Medicine) and cancer care (e.g., Clinical Oncology Society of Australia) [37–43]. Typically, guidelines advise people living with and beyond their cancer to engage in at least 150 min of moderate-to-vigorous physical activity per week, which can take the form of structured, purposeful exercise [14, 41, 43, 44]. Recent guidelines emphasize that moderate-to-vigorous exercise and physical activity can be achieved through a combination of aerobic, resistance and flexibility exercises, and supervised interventions are most effective [45–48].

However, despite consistent evidence that regular structured exercise can help cancer patients to better manage the acute- and long-term disease- and treatment-related effects on their health and well-being, research suggests up to 70% of cancer patients do not reach the recommended levels of moderate-to-vigorous physical activity [30, 49–52]. In fact, these patients undergo a sustained reduction in their physical activity levels following diagnosis, which can persist years after treatment remission [53–55]. Reasons cited for low engagement in physical activity include social and environmental barriers to engaging in supervised exercise, such as transportation costs and accessibility, financial problems, time, and distance to a training facility. To address such barriers, home-based unsupervised physical activity programs have been proposed with guidance provided by instruction booklets [56–61]. However, even though home-based programs offer a more flexible, feasible, and accessible option for increasing physical activity levels among cancer patients, poor uptake and low adherence remain a challenge [42, 62–67]. Therefore, alternative interventions that have the potential to engage and motivate people living with cancer to adopt and maintain an active lifestyle are critical. In this sense, group-based exercise interventions seem to facilitate greater improvements in overall quality of life when compared with personal training intervention [68]. However, further studies are needed to clarify the effects of a group-based exercise for encouraging incorporation of an active lifestyle and improving health and physical functioning in cancer survivors.

Based on current strategies to encourage exercise engagement and referral as regular practice for cancer survivors [69–73], we designed a randomized trial to test the impact of a supervised group exercise intervention combined with booklet recommendations compared with unsupervised physical activity at home following booklet recommendations among breast cancer survivors. We hypothesize that exercise supervision in a group model is a key parameter for encouraging both the adoption and adherence to exercise, and thus sustaining an active lifestyle leading to improvements in global health, physical functioning, and quality of life.

## Study aim and objectives

The aim of the study is to assess the impact of a 16-week supervised group exercise intervention, combined with physical activity recommendations delivered via a booklet, on overall physical activity, physical functioning, and quality of life among breast cancer survivors. The primary outcome includes aerobic capacity (assessed via directly measured peak oxygen consumption, or VO_2_)_._ Secondary outcomes are physical activity (assessed via accelerometry and questionnaire), physical functioning (assessed via muscle strength, balance, and agility), self-reported quality of life, fatigue, presence of lymphedema, body composition, immune function, adherence to physical activity guidelines, and perceptions of self-image.

Additionally, we will investigate whether supervised aspects of the intervention enhanced participants’ motivation for physical activity and exercise, and whether changes in motivation are linked to adherence to exercise program and higher levels of physical activity overall.

## Methods

### Study design

The present study is a prospective, longitudinal, pre-post-intervention (Fig. 1), open-label, active-controlled randomized superiority trial with participants allocated into two parallel-groups:
Supervised group: canoeing and physical activity recommendationsUnsupervised group: home-based physical activity recommendations

**Fig. 1 Fig1:**
[figure not shown]
Overall design of the study

Our hypothesis is that the supervised group exercise intervention combined with physical activity recommendations will achieve better adherence to active lifestyle, exhibiting greater improvements in global health, physical functioning, and quality of life than the unsupervised intervention. Both groups will receive advice on adopting an active lifestyle, based on standard physical activity recommendations established by the World Health Organization (WHO). The advice will be provided verbally in a meeting (see section “Participant randomization and group allocation”) and via a booklet containing physical activity recommendations produced by the Cancer Institute of the State of Sao Paulo (ICESP). Both groups will be advised on increasing general daily movement (e.g., commuting, home-based activities, and leisure time physical activity) and undertaking at least 150 min per week of structured exercise (i.e., aerobic, strength, or flexibility), trying to exceed these recommendations by any movement including physical therapy, gym, sports, structured exercises, and not structured physical activity, discriminating the activities with specific questionnaires applied every 2 weeks during intervention. Participants in the supervised group will take part in group canoeing training sessions twice a week, while the unsupervised group will engage in physical activity and exercise of their choice. Considering the standard delivery of physical activity recommendations adopted in cancer centers to promote an active lifestyle, the unsupervised group is taken as the control group in this study. Adherence to the WHO physical activity recommendations outlined in the booklet will be monitored every 2 weeks throughout the 16-week intervention period in both groups via a standardized questionnaire, which will be completed in-person by participants in the supervised group and via telephone call in the unsupervised group. The findings from this study will be reported in accordance with the recommendations of the Consolidated Standards of Reporting Trials (CONSORT) guidelines as described in the section “Discussion”.

### Ethical compliance

This study protocol is registered in a database of clinical research studies (Brazilian Registry of Clinical Trials - ReBec) under the number RBR-3fw9xf and was approved by local Ethical Committees (Research Ethics Committee of the USP School of Physical Education and Sports approval: 2.441.435, and Commission of Ethics in Research in Human Beings of the USP Medical School approval: 2.836.680). This manuscript is described according to the Standard Protocol Items: Recommendations for Interventional Trials (SPIRIT) checklist (Fig. 2, Additional file 1) and the study is performed in accordance with the ethical principles laid down in the seventh and current edition (2013) of the Declaration of Helsinki.

**Fig. 2 Fig2:**
[figure not shown]
Overall schedule of enrollment, intervention, and assessments following the Standard Protocol Items: Recommendations for Interventional Trials (SPIRIT)

Participants who meet the eligibility criteria and have been authorized for participation will receive a detailed explanation about the protocol and provide written consent, including storage of biological specimens. Participants will be informed that they can withdraw from the study at any time without consequence. The intervention will be discontinued for the participants who 1) request to stop, 2) have any surgery scheduled, or 3) suffer any injuries that prevent the practice of physical activity or exercise. The reasons for drop-out will be recorded and all data collected from these participants will be included in the analysis. From the time point of discontinuation, no outcome will be collected from those participants. The protocol poses a low risk to the participants regarding blood sampling and cardiorespiratory evaluation. Both procedures will be performed by an experienced physician ([name]) and participants will be monitored after the cardiorespiratory fitness test until they fully recover from the exercise bout. During the canoeing or exercise training sessions, participants will always wear life jackets, and if they feel any discomfort, they will receive local medical care and will be taken to the nearby University Hospital if needed. Likewise, all participants will continue their routine medical care at ICESP.

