### Assessments

The experimental procedures described below will be performed at baseline (Pre) and after 16 weeks of the intervention (Post), keeping an interval of 3 or 4 days after the last canoeing training session. An exception will be the evaluation of physical activity engagement (time, frequency, and intensity), which will also be monitored at 8 weeks (mid-way point of the intervention). The assessment protocol will be divided into two visits and all procedures will take place at the School of Physical Education and Sport of the University of Sao Paulo (Fig. 3). Participants will be advised to avoid performing physical activities and alcohol ingestion in the 24 h prior to the visits, to refrain from tobacco use and stimulant beverages (coffee, tea) for at least 6 h, and to take their medication as recommended by their physicians. In the first visit, the participants will arrive at 7 am, following an 8-h fasting period and undertake the procedures in the following order: 1) blood sampling; 2) anthropometry and lymphedema measurement; 3) eat a snack consisting of an apple, 150 g of salted crackers, and 200 ml of juice; and 4) cardiorespiratory fitness test. The second visit will take place at least 2 days later to allow the participant to fully recover from the fitness test. For the second visit, the participants will arrive at 7 am and undertake the following evaluation: 1) questionnaires assessing quality of life in cancer survivors, health status, fatigue, body image, and physical activity motivation; and 2) physical functioning tests.

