#### Data analysis

The data analyst will receive the raw data coded for participant names and group allocation after completion of data collection. Group allocation will be unblinded after termination of data analyses. The Shapiro–Wilk and Levene’s tests will be used to determine normality and variance equality, respectively, and non-normal scale data will be log transformed. If the transformation does not produce a normal distribution, residual analyses will be performed to test if influential points change the interpretation of the results. If interpretations change, these points will be manually removed. Linear mixed models having group and time as fixed factors and participants as a random factor will be performed for each dependent variable [maximal aerobic capacity (VO_2_ max), daily physical activity, and adherence to physical activity guidelines (assessed via accelerometry and questionnaire), physical functioning (assessed via muscle strength, balance, and agility), self-reported quality of life, fatigue and perceptions of self-image (assessed via specific validated questionnaires), presence of lymphedema, and body composition and immune function]. Baseline differences in outcomes will be examined by independent *t*-test. An analysis of covariance (ANCOVA) will be implemented including the baseline variable as a covariate, group as a fixed factor, and participants as a random factor, in case of differences in baseline values between groups. An intention-to-treat analysis will also be performed in case of a high incidence of missing values, using linear mixed models; the first analysis will be performed removing the missing values, while the second analysis will be performed incorporating the missing data points to determine the impact of missing values in the overall results [96]. Whenever a significant F-value is obtained, a post hoc test with Tukey’s adjustment will be performed. Ordinal data will also be analyzed using mixed models having group and time as fixed factors, and participants as random factor. Nominal data will be compared using chi-square distributions and significance will be determined by residual analyses (< − 2 or > 2).

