**Fig. 4 Fig4:**
[figure not shown]
Consolidated Standards of Reporting Trials (CONSORT) flow diagram summarizing the trial status

Prior to commencing the main trial, we conducted a small-scale pilot study to examine potential barriers to recruitment and the feasibility of protocol delivery. From this study, we learned that most of the participants in the unsupervised physical activity recommendations group did not answer phone calls during the intervention. Likewise, we acknowledge that some participants of this study neither did not have access to the ICESP booklet nor remembered to follow it, even though it is commonly used as a guideline by the Cancer Institute. Thus, to minimize these issues, we amended the protocol to include a standard talk about the benefits of physical activity for people living with cancer, immediately after the randomization. Furthermore, following the pilot study, we included the assessment of physical activity via accelerometry at the mid-intervention point (week 8), to provide a greater insight into change in physical activity behavior during the intervention. These procedures are meant to promote retention and complete follow-up of the participants.

Recruitment for the main trail has now commenced, and barriers identified to date include participants not found or not willing to take part, distance from the canoe training center (too far to travel), limitations imposed by the conventional therapy, movement restriction, and clinical clearance, among others. In addition, some barriers are observed once participants are recruited to the intervention, including requirement for mammary reconstruction surgery and distance from the canoe training center, which impact participants’ attendance to supervised exercise sessions. Regarding these barriers, the study staff will use all plausible means to overcome the limitations and support willing participants to continue in the study.

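### Outcome collection ends when a woman stops the intervention, so the as-randomised effect on peak VO2 rests on an untestable missing-data assumption

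*Protocol article*

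**What the plan says.** The rule stands in the Ethical compliance section of the protocol article, in the paragraph after the Fig. 2 caption. It first lists who stops: "The intervention will be discontinued for the participants who 1) request to stop, 2) have any surgery scheduled, or 3) suffer any injuries" that prevent physical activity or exercise. It then says "The reasons for drop-out will be recorded and all data collected from these participants will be included in the analysis", and continues: "From the time point of discontinuation, no outcome will be collected from those participants". The right to withdraw from the study is mentioned just before, but the rule does not distinguish a woman who withdraws from one who only stops exercising.

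Under Assessments, the experimental procedures "will be performed at baseline (Pre) and after 16 weeks of the intervention (Post"). The only exception is physical activity engagement, which is also measured at week 8. Peak VO2 therefore has one baseline and one follow-up value.

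Data analysis plans an intention-to-treat mixed model if many values are missing, run once without the missing values and once "incorporating the missing data points to determine the impact of missing values".

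The Discussion names barriers seen after recruitment, "including requirement for mammary reconstruction surgery and distance from the canoe training center", and says that they affect attendance at supervised sessions. Of the changes made after the pilot it says: "These procedures are meant to promote retention and complete follow-up of the participants".

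**The concern.** Stopping an exercise programme and leaving a trial are different events. The rule merges them, so a woman who gives up the programme but would gladly return for a week-16 test is not tested. What is kept from her is a baseline VO2, which says nothing about her change.

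This bears directly on the trial's question. The hypothesis is that supervision in a group improves adherence and, through it, fitness and health. The women who stop are those in whom the strategy did not hold. If they are left unmeasured, the comparison leans on those who stayed, and the article's own aim of complete follow-up is undercut. A value that was deliberately not collected cannot be restored at the analysis stage.

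**Working it through.** **1. What a discontinuer contributes.** Her baseline VO2 is observed and her week-16 VO2 is not. There is no intermediate VO2. Under a mixed model with group and time, her week-16 value is in effect predicted from the completers of her own arm, given her baseline. That is the missing-at-random assumption. Stopping because of injury, surgery or unwillingness may well go with a poorer change in VO2 than baseline predicts, and no observed VO2 can test this.

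**2. The plan's own figures.** Inputs from Power calculation and sample size: power 0.90, alpha 0.05, pre-post correlation 0.50, 15 per group, raised by 20%. The last step reproduces: 15 × 1.20 = 18. The 15 cannot be reproduced forward because the article gives no numerical effect size.

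**3. Back-solved effect (an inference, not a figure in the documents).** For the repeated-measures interaction with two groups and two times, λ = f² × N × 2 / (1 − 0.50), with N − 2 denominator degrees of freedom. Power of 0.90 at N = 30 requires f ≈ 0.307 (λ ≈ 11.28). In a 2 × 2 layout f = d/4, so d ≈ 4 × 0.3066 ≈ 1.23 SD difference in change. At correlation 0.50 the SD of change, √(2 × 0.50), equals 1 SD of a single measurement.

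**4. Bias formula.** Let q be the proportion stopping in an arm and s the shortfall of stoppers' change against that arm's completers, not explained by baseline. Each arm's as-randomised mean change is the completers' mean minus q × s. The bias in the completers' contrast (subscript 1 supervised, 0 unsupervised) is therefore q₁s₁ − q₀s₀.

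**5. One-sided illustration.** Assume that supervised stoppers keep no benefit over control (s₁ = 1.23) and that nobody is lost from the other arm (q₀ = 0). The as-randomised effect is then (1 − q₁) × 1.23 and the overstatement factor is 1/(1 − q₁).

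| Supervised stopping | As-randomised effect (SD) | Completers overstate by |
|---|---|---|
| 10% | 1.10 | 11% |
| 20% | 0.98 | 25% |
| 4 of 18 (22%) | 0.96 | 29% |
| 30% | 0.86 | 43% |
| 40% | 0.74 | 67% |

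(The 4 of 18 row is 14/18 × 1.23; with the unrounded 1.226 it is 0.95.)

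**6. Less extreme illustrations.** With 30% against 10% stopping and the same shortfall of 0.5 to 1.0 SD in both arms, the bias is 0.5 × 0.20 = 0.10 to 1.0 × 0.20 = 0.20 SD. With equal loss and equal shortfall it is 0. If the larger loss were in the unsupervised arm, the sign would reverse.

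**7. Power.** At 1.23 SD, 15 against 15 completers gives 0.90. With 14 against 18, the harmonic mean is 2 × 14 × 18 / 32 = 15.75 per group and power is about 0.92. With 14 against 14 it is 0.88.

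**The case against.** Four stronger readings are tempting, and the documents do not support them.

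- **That the as-randomised effect cannot be estimated at all.** Data analysis plans a mixed model that includes women with missing values, which gives an estimate under missing at random. The weakness is that the assumption is untestable and doubtful. If few women stop, little is lost.
- **That losses will fall on the canoeing arm.** The triggers apply to both arms, reconstruction surgery can occur in either, and both arms travel to the campus for assessments. The Discussion reports poorer attendance, and missing sessions is not itself a trigger: a woman who skips sessions without asking to stop still has her week-16 test. The pilot's arm-specific problem was unanswered calls in the unsupervised arm. What stands is that unequal loss is plausible, since only one arm has fixed sessions to travel to twice a week.
- **That 14 women left in one arm, below the required 15, means a power shortfall.** It does not while the other arm keeps 18.
- **That 25% or 29% is the expected bias.** It is one end of a range. It assumes loss in one arm only and no retained benefit, and it uses an effect size that the article does not print.

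It is also fair to say that some women who stop for injury or surgery could not do a treadmill test taken to exhaustion. For VO2 the gain lies mainly with those who stop for other reasons and agree to return. None of this supplies a reason for not inviting them.

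**Conclusion.** The point holds as an explicit rule that damages the primary comparison, not as something a condensed article left out. Every woman who discontinues early lacks a follow-up VO2, and the planned mixed model covers her only by assuming that she changed as completers with her baseline did.

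The size is unknown, because the article gives neither an effect size nor discontinuation rates by arm. Under the back-solved 1.23 SD, the illustrations run from about zero (equal loss, equal selection), through 0.10 to 0.20 SD (30% against 10% loss), to about 0.27 SD (1.23 − 0.96) when 4 of 18 supervised women stop, keep no benefit and nobody is lost from the other arm. The direction depends on which arm loses more. Loss of precision is modest; bias is the harm.

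**What to change.** Replace the sentence on outcome collection with wording such as: *Women who stop the intervention remain in the study and are invited to the scheduled week-8 accelerometry and week-16 assessments, unless they withdraw consent for follow-up. Where a test is medically not permitted, the remaining assessments are still collected.* Record discontinuation of the intervention and withdrawal from follow-up as two separate events, each with date and reason. The rules for stopping the intervention stay as they are.

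The cost is a protocol amendment and revised consent wording; the visits are already in the schedule. Some women will decline or be unable to do the treadmill test. Recruitment began in June 2018, so data already missed cannot be recovered, but the article describes recruitment as not yet complete and later participants would benefit. The as-randomised effect may also prove smaller than the one the trial was sized for. In the one-sided illustration with 20% stopping and all 36 measured, power would be about 0.82, slightly optimistic because the SD is held at 1. The present rule hides that dilution; it does not avoid it.
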